**Main variables**					
Knowledge and understanding of the procedure	12-point specific multiple-response questionnaire for each procedure (see Appendix 3)	1st	2nd	3rd	
Satisfaction with the method of communicating information	10-point VAS^b^	1st	2nd	3rd	
Satisfaction with information transmitted	10-point Visual Analog Scale^b^	1st	2nd	3rd	
Anxiety related to the procedure	STAI questionnaire and 10-point VAS^b^	1st	2nd	3rd	
**Other variables**					
Demographic variables	Sex, age, marital status, and educational level	1st			
Personal history	Previous IR procedures, other types of interventions, history of anxiety and depression, and previous knowledge of IR	1st			
Procedure-specific variables	Preparation method, anesthesia type, sedation level (Ramsay Sedation Scale), and procedure duration				4th
Pain intensity during the procedure	10-point VAS^c^				4th
Intervention tolerance level	10-point VAS^b^				4th
Satisfaction level with the intervention	10-point VAS^b^				4th
Usefulness of explanatory videos	10-point VAS^b^ and dichotomous questions^d^		2nd		

*IR* Interventional radiology, *STAI* State-Trait Anxiety Inventory, *VAS* Visual analog scale

^a^ Data collection times: 1st (screening visit), 2nd (after the consultation with the radiologist, only for the experimental group), 3rd (on the day of the procedure, before it is performed), and 4th (on the day of the procedure, after it is performed)

^b^ VAS, where 1 represents the minimum value and 10 the maximum value

^c^ VAS for pain, where 0 indicates no pain, 1–3 mild pain, 4–6 moderate pain, 7–8 severe pain, and 9–10 excruciating pain

^d^ The questions are: Did you find the video useful for better understanding the intervention? Did you like the video as an explanatory tool? Do you feel less anxiety after watching the video? Do you understand the intervention better after watching the video?

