## Objectives and study design

The CLINTERVENTIONAL study is a single-center, two-arm RCT, registered at clinicaltrials.gov (NCT05461482). In the control arm, patients will be informed about the IR procedure by the ordering physician, which is the usual process in the hospital. In the experimental arm, patients will have an additional consultation with an interventional radiologist and will be shown an explanatory video about the procedure. This trial is independent of industry funding. It has been initiated and conducted with resources from the Maimónides Biomedical Research Institute of Córdoba and Reina Sofía University Hospital (Córdoba, Spain). The study protocol, informed consent form template, and other requested documents regarding both the scientific content and compliance with applicable regulations regarding research and human subjects have been reviewed and approved by the Research Ethics Committee of Córdoba. The trial will be conducted in accordance with the Declaration of Helsinki.

Participants will receive a clinical trial information sheet and must provide written informed consent (Appendix 1: Clinical trial information sheet and sample informed consent form). The allocation of patients will be done using random number tables with a 1:1 allocation ratio. The participants, data analysts, and outcome evaluators will be blinded to the arm assignment.

The main objective is to assess and compare both groups at baseline and after the IR procedure in terms of patients’ level of knowledge and understanding of the IR procedures, patients’ satisfaction with the information provided and the method of communication, and patients’ anxiety

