**Fig. 1 Fig1:**
[figure not shown]
Flowchart illustrating the study design, showing a schematic summary of critical time points throughout the trial

After their cases have been presented to a multidisciplinary board or discussed between physicians, patients will be informed about the IR procedure (objectives, benefits, risks, alternatives, etc.) by the ordering physician, according to the usual procedure in our hospital. Next, patients will be seen by the trial coordinators, who will inform them about the clinical trial, invite them to participate, and explain the informed consent procedure. After that, subjects who agree to participate will be randomly assigned to the control group (in which no more information will be provided) or to the experimental group. Randomization will be conducted by an independent coordinator using random number tables specific to each procedure included in the study.

Subjects in the experimental group, in addition to receiving the same information as the control group, will have a consultation with an interventional radiologist, who will explain the IR procedure in detail. Subjects in the experimental arm will also be given a leaflet that explains the preparation for the procedure, its objectives, the expected benefits and associated risks, and what they can expect once it is performed. In this leaflet, a QR code will take patients to an animated video that explains this information in a clear, easy-to-understand format. Eight videos have been made, one for each type of procedure included in the trial (endovascular recanalization, placement of tunneled central venous catheters, fistulograms, and endovascular repair of hemodialysis fistulas, endovascular embolization, percutaneous biopsies, percutaneous drainage of collections, percutaneous transhepatic biliary drainage, and percutaneous nephrostomies), which last approximately four minutes each. See Appendix 2: leaflets with QR codes enabling access to the corresponding videos—one for each IR procedure.

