The variables that will be analyzed, the methods used to evaluate them, and the different points in time in which they will be analyzed are shown in Table 2. Knowledge and understanding of the interventions will be assessed by means of 12-question multiple-choice questionnaires. The scoring system for these questionnaires awards 1 point for each correct answer. The questionnaires consist of five blocks of questions: those regarding the procedure itself, preparation, benefits, risks, and care following the procedure. These questionnaires have been developed following a systematic approach to ensure their validity and reliability. A comprehensive literature review was first conducted to identify relevant items used in similar studies [12–16]. A preliminary version was then prepared, which was discussed and revised by all authors, adjusting it to fit the study’s purpose. Finally, a pilot test was performed with a sample of 16 patients who met the selection criteria. During this phase, patients provided feedback through structured interviews, which allowed adjustments to be made to improve the clarity and applicability of the questionnaires. The final validated version of the questionnaires is presented in Appendix 3.

**Table 2 Tab2:** Variables, measurement method, and data collection times

Variables	Measurement method	Data collection time^a^			

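### Only the experimental arm sits the main-outcome questionnaires an extra time before the between-arm comparison, so any effect of that sitting is confounded with the intervention

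*Protocol article*

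**What the plan says.** Under its main variables, Table 2 lists knowledge, satisfaction with the method of communication, satisfaction with the information, and anxiety, each at the 1st, 2nd and 3rd times. One instrument is named per variable for all times. Knowledge uses a "12-point specific multiple-response questionnaire for each procedure (see Appendix 3"), whose scoring "awards 1 point for each correct answer". Anxiety uses "STAI questionnaire and 10-point VAS". No parallel form is stated.

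Footnote a defines the times. The 1st is the screening visit, the second is "2nd (after the consultation with the radiologist, only for the experimental group"), and the third is "3rd (on the day of the procedure, before it is performed"). The 4th follows the procedure, and no main variable is marked there.

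Study cohort and outcome measures describes the comparator as the "control group (in which no more information will be provided"). Objectives and study design states the contrast of interest: "The main objective is to assess and compare both groups at baseline and after the IR procedure".

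**The concern.** The trial sets out to estimate the effect of the consultation and explanatory material. The schedule adds a further difference between the arms: one more administration of the outcome instruments, in the experimental arm only, before the final comparison. The extra sitting is nowhere described as part of the intervention.

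This matters most for knowledge. A fixed multiple-choice test repeated in the same form can be answered somewhat better simply because it has been seen more often. It also tells patients which topics will be asked, and the leaflet and video cover closely related topics. A gain from that source would be added to the estimated effect on the outcome for which the trial is powered, where the target difference is only 1 point.

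**Working it through.** **1. Administrations per arm, from Table 2 and footnote a**

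| Time | Experimental | Control |
|---|---|---|
| 1st (screening) | main variables | main variables |
| 2nd (after consultation) | main variables and video items | none |
| 3rd (before procedure) | main variables | main variables |
| 4th (after procedure) | no main variable | no main variable |
| Sittings before the 3rd | 2 | 1 |

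The main objective speaks of a comparison after the procedure, but Table 2 collects no main variable then. The final between-arm comparison can only use the 3rd time.

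**2. Can the planned analysis separate the two effects?** Every experimental patient is scheduled for the 2nd sitting and no control is, so the indicator for extra testing equals the indicator for arm. The t-tests and mixed analysis of variance in Data collection and statistics cannot estimate them separately. The 2nd measurement has no control counterpart and adds nothing to the randomised contrast.

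**3. The plan's own sample size.** Inputs from Data collection and statistics: difference 1, SD 3.5, two-sided alpha 0.05, power 0.80, ratio 1:1, loss 10%.

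n per arm = 2 × [3.5 × (1.960 + 0.842) / 1]² = 192.3, so 193 evaluable. With loss, 192.3 / 0.9 = 213.7, so 214. The stated figure is reproduced (rounding to 193 first would give 215).

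**4. Sensitivity to a retest gain.** Let b be the mean gain in knowledge score at the 3rd time from having had two earlier sittings rather than one, and let the true intervention effect be zero. The documents give no value for b, so the values below are assumptions.

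SE = 3.5 × √(2/193) = 0.356

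P(p < 0.05) = 1 − Φ(1.96 − b/SE) + Φ(−1.96 − b/SE)

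| Assumed b (items of 12) | b/SE | P(p < 0.05) |
|---|---|---|
| 0 | 0 | 5.0% |
| 0.1 | 0.28 | 5.9% |
| 0.25 | 0.70 | 10.8% |
| 0.5 | 1.40 | 28.9% |
| 0.75 | 2.11 | 55.8% |

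Whatever the true effect, b is added to its estimate.

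**The case against.** Several counter-arguments have force.

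- *Direction.* A reader might infer that all the main outcomes are biased towards the experimental arm. The documents do not support that. Learning from retesting is plausible for a knowledge test, but there is nothing to learn on a satisfaction scale, and repeated anxiety measurement could move scores either way. The directional claim is confined to knowledge.
- *Mechanism.* A reader might picture patients noticing which items they missed and then looking up the answers at home. No feedback on answers is described. Table 2 collects the video ratings at the 2nd time, so the video appears to have been watched by then. Later viewing through the QR code remains possible, but the point does not need it: familiarity with the items is enough.
- *Size.* Controls have also sat the test once, so only the increment of a second earlier sitting counts. At 0.1 item the error rate is close to nominal. Nothing in the documents shows that the upper values in the table occur.
- *Purpose.* The 2nd time holds the data for the fourth secondary objective, the evaluation of the videos. This stands, and the video items should stay. The within-group objective, however, is defined from the beginning of the trial to its end and does not need an intermediate value of the main variables.

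None of this answers the central point. The asymmetry is stated outright in the schedule, so it is not a detail left to a fuller document, and it coincides exactly with arm.

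**Conclusion.** The point holds as a confounding of assessment schedule with treatment at the only shared post-randomisation assessment of the main outcomes. For knowledge the likely direction favours the experimental arm; for satisfaction and anxiety it is unknown. On assumed gains of 0.1 to 0.75 item, with SD 3.5, 193 evaluable per arm and no true effect, the chance of a significant knowledge result runs from about 6% to 56% against a nominal 5%. These figures illustrate sensitivity. They do not estimate the bias, and they do not show that a positive result would be false. Randomisation and the shared 1st and 3rd assessments are sound. The case for acting is that the planned analyses cannot separate the two effects and the remedy is cheap.

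**What to change.** Amend Table 2 so that knowledge, both satisfaction scales and anxiety are collected at the 1st and 3rd times only, in both arms. Keep only the video-usefulness items at the 2nd time. The cost is the immediate post-consultation value, which has no control counterpart; patient burden falls and the sample size stays at 214 per arm.

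If the intermediate value is wanted, give controls the same instruments at a matched interval after the 1st time. The cost is a small added burden for controls.

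If patients have already been measured at the 2nd time, any sensitivity analysis should restrict both arms to patients randomised after the change. Dropping only the experimental patients who had the extra sitting would set later experimental patients against all controls and break the randomised comparison. For those enrolled earlier, report the unequal number of sittings as a limitation.

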### Data collection and statistics

Trained research coordinators will supervise the questionnaires without participating in clinical care. Data collection will be conducted with digital and paper questionnaires. The results will then be uploaded into a dedicated database and organized for data extraction. Data managers will be responsible for data entry. To ensure robust data quality control, a subset of patients will be randomly selected for double data entry. This meticulous approach serves as the primary mechanism for validating data accuracy, with thorough verification procedures used to address any inconsistencies identified. The information collected will remain anonymous; a three-digit code will be used to identify patients. The data will be retained for at least 25 years after completion of the study, in compliance with regulations. Digital files will be stored on institutional computers and protected with passwords, while paper copies of the questionnaires will be securely stored at research facilities.

Descriptive statistics will be used to calculate absolute and relative frequencies for qualitative variables and mean and standard deviation for quantitative variables. Confidence intervals with 95% confidence intervals will be calculated.

For comparisons of quantitative variables, parametric tests will be used if the data will follow a normal distribution: Student’s *t*-test for independent data and a one-way analysis of variance when comparing independent groups and Student’s *t*-test for paired samples and repeated measures analysis of variance in the case of paired samples. In addition, a mixed analysis of variance will be performed to compare intragroup and intergroup variability at the same time. If the data do not follow the normal distribution, nonparametric tests will be used. For comparisons of qualitative variables, the *χ*^2^ test will be used for comparisons of independent data and the McNemar’s test and Cochran’s *Q* test for paired samples.

Finally, a multiple logistic regression analysis (manual stepwise method) will be performed in order to obtain an associative model among the variables of pain intensity during the procedure, level of tolerance of the procedure, and satisfaction with the intervention and the rest of the covariates potentially considered as such.

All comparisons will be two-tailed and considered significant when *p* < 0.05. The data will be stored, processed, and analyzed using SPSS® Version 28.0 (IBM, Armonk, NY, USA).

The sample size has been calculated using the GRANMO sample size calculator. Based on a study by Lattuca et al [13], a difference equal to or greater than 1 on the knowledge and understanding score (standard deviation, 3.5) was assumed. Hence, the estimated effect size (Cohen’s *d*) was 0.285. Additionally, a bilateral design, an alpha risk of 0.05, a beta risk of 0.2, an allocation ratio of 1, and a loss-to-follow-up rate of 10% were established. Therefore, 214 subjects in the control group and 214 in the experimental group would be required. No strategies will be used to foster quicker enrollment.

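### The between-arm tests leave the collected baseline out as a covariate and let the distribution of the data choose the test; a baseline-adjusted linear model would be more efficient at no cost

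*Protocol article*

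**What the plan says.** The section on data collection and statistics gives the independent-samples t-test or one-way analysis of variance for comparing groups when the data are normal. Otherwise: "If the data do not follow the normal distribution, nonparametric tests will be used". It does not name those tests. It then adds that "a mixed analysis of variance will be performed to compare intragroup and intergroup variability at the same time". The only model with covariates is a stepwise logistic regression for pain, tolerance and satisfaction with the intervention, none of which is a main variable.

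The main objective is to "assess and compare both groups at baseline and after the IR procedure" on knowledge, satisfaction and anxiety. Table 2 schedules each of these main variables at the 1st, 2nd and 3rd times. Its footnote a describes the middle one as "2nd (after the consultation with the radiologist, only for the experimental group"; the 3rd is on the procedure day, before the procedure.

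The sample size rests on the knowledge score: "a difference equal to or greater than 1 on the knowledge and understanding score (standard deviation, 3.5) was assumed". The other inputs are "an alpha risk of 0.05, a beta risk of 0.2, an allocation ratio of 1, and a loss-to-follow-up rate of 10% were established", and the result is that "214 subjects in the control group and 214 in the experimental group would be required".

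**The concern.** Three features of the stated analysis sit badly together.

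- Each main variable has a 1st-time value in both arms, yet no stated between-arm test uses it as a covariate. If baseline predicts the later score, precision that has already been paid for is left unused.
- The choice between a parametric and a nonparametric test depends on the trial data. The two kinds of test answer different questions: a t-test estimates a difference in means, which is what the trial was sized on, while a rank test does not.
- The mixed analysis of variance stands beside these tests without a stated rank among them. Between arms it can use only the 1st and 3rd times, because controls have no 2nd measurement.

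At stake are the precision of the main comparison and a single answer, fixed in advance, to the question the trial asks. A final-score t-test, a test of change and a rank test can disagree on the same data.

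**Working it through.** **Inputs from the article:** difference 1 point, SD 3.5, two-sided alpha 0.05, power 0.80, 1:1 allocation, 10% loss, 214 per arm. **Assumptions:** 3.5 is the SD of a single score and is equal at the 1st and 3rd times; the correlation r between those times is 0.3, 0.5 or 0.6. The article gives no r.

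**Step 1: reproduce the stated size.** For two independent means, n per arm = 2 × (1.96 + 0.8416)² × 3.5² / 1² = 2 × 7.849 × 12.25 = 192.3, or 193 evaluable. Allowing for loss, 192.3 / 0.9 = 213.7, or 214. The stated figure reproduces. It is a calculation for one time point, with no baseline term.

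**Step 2: effective SD under each analysis.**
- Final-score t-test: 3.5, whatever r is.
- Change score, equivalent to the group-by-time test of a mixed analysis of variance on the 1st and 3rd times: 3.5 × √(2(1 − r)).
- ANCOVA on the 1st-time value: 3.5 × √(1 − r²).

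**Step 3: power.** With 193 per arm, power = Φ(1 / (SD × √(2/193)) − 1.96), where √(2/193) = 0.1018.

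| r | Final-score t-test | Change / group-by-time | ANCOVA |
|---|---|---|---|
| 0.3 | SD 3.50, 80% | SD 4.14, 66% | SD 3.34, 84% |
| 0.5 | SD 3.50, 80% | SD 3.50, 80% | SD 3.03, 90% |
| 0.6 | SD 3.50, 80% | SD 3.13, 88% | SD 2.80, 94% |

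For example, ANCOVA at r = 0.5 has standard error 3.03 × 0.1018 = 0.309, and 1/0.309 − 1.96 = 1.28, which gives 90%.

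**Step 4: precision.** The half-width of the 95% confidence interval is 1.96 × 3.50 × 0.1018 = 0.70 points for the final-score t-test. For ANCOVA it is 0.67, 0.60 and 0.56 points at r = 0.3, 0.5 and 0.6.

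**Step 5: if nobody is lost.** With 214 analysed per arm, the final-score t-test has 84% power and ANCOVA has 87%, 93% and 96%. The group-by-time test has 70.5%, 84% and 91%, and it reaches 80% at r of about 0.44 rather than 0.5.

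In both settings ANCOVA is at least as powerful as either alternative at every r shown. The final-score test beats the change test below r = 0.5 and loses to it above, so choosing between those two is a bet on an unknown correlation. ANCOVA removes the bet. These figures take no credit for adjusting for procedure type.

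**The case against.** The strongest reply is that nothing here is invalid. A t-test in a randomized trial is a sound analysis. The 80% in the article belongs to exactly that test, and the test delivers it at any r. A condensed article may also leave the primary model and its covariates to a statistical analysis plan that is not shown. The first part stands in full. The second stands only in part, because the article does name its tests, so a different primary model would replace a published method.

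Four stronger readings are tempting, and the document does not support them.

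- *The trial is underpowered.* The mixed analysis of variance is introduced as an addition, with no power stated for it. Its shortfall depends on an assumed r below 0.5; at 0.6 it does better than the final-score t-test. The group main effect of that analysis would have low power, because it averages in the baseline, but no section names it as the treatment test.
- *The mixed analysis of variance would drop every control.* That would follow only if it were run over all three times. The article does not say so, the main objective needs only two, and the 2nd time can serve the within-group objective.
- *Baseline is ignored altogether.* The group-by-time test does use it, through change. What is missing is baseline as a covariate.
- *The normality rule is bound to lead to rank tests.* In simulated samples of 193 from bounded, rounded scores, the Shapiro-Wilk test rejected normality every time. However, those distributions were chosen for the exercise, they did not include the State-Trait Anxiety Inventory, and the article names no formal normality test. The nonparametric tests are also left open, and one applied to change scores would use baseline.

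**Conclusion.** The point holds as a recommendation on efficiency and on fixing the analysis in advance, not as an error in the sample size. At the planned 193 evaluable per arm, adjusting for the 1st-time value raises power on the knowledge score from 80% to about 84%, 90% or 94% at r = 0.3, 0.5 or 0.6. This rests on an SD of 3.5 for a single score, equal at both times, and on correlations the article does not give. If 3.5 were the SD of a change, the comparison with the mixed analysis of variance would fall away.

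Two parts need no assumed correlation: the test is chosen from the data, and any rank test reached that way no longer estimates the 1-point mean difference behind the sample size. At about 193 per arm, inference on a mean difference does not need normally distributed raw scores, so the rule offers little protection for the ambiguity it creates. The change should be made.

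**What to change.** For each main variable, name one primary between-arm analysis: a linear model of the 3rd-time value on arm, 1st-time value and procedure type, with heteroscedasticity-robust standard errors. Procedure type belongs in the model because randomization uses separate tables for each procedure; the knowledge questionnaire is also procedure-specific. Report the adjusted mean difference with its 95% confidence interval whatever the distribution looks like.

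Keep rank tests as sensitivity analyses. The mixed analysis of variance is then not needed for the between-arm question. Use the 2nd-time data only for description within the experimental arm. State that the 3rd time is the endpoint: Table 2 places it before the procedure, while the main objective speaks of a comparison afterwards, so the two should be aligned.

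The cost is wording in the protocol and the statistical analysis plan. ANCOVA is available in the named software, and no new data or patients are needed.

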There are four secondary objectives. The first is to analyze changes within each group in patients’ level of knowledge and understanding of the IR procedures, patients’ satisfaction with the information provided and the method of communication, and patients’ anxiety at the beginning of the RCT and at the end. The second is to analyze and compare the duration of the intervention, the patients’ perceived pain intensity during the procedure, the level of tolerance for the intervention, and the patients’ satisfaction level with the intervention performed. The third is to evaluate the association of different variables (demographics, personal history, assigned arm, type of IR procedure, anxiety related to the IR procedure, knowledge and understanding of the IR procedure, type of anesthesia, and degree of sedation) with the intensity of pain during the intervention, tolerance of the procedure, and satisfaction with the intervention. The fourth is to evaluate explanatory videos as an educational tool.

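### Pain, tolerance and satisfaction are recorded as VAS scores, but the plan models them by manual stepwise logistic regression with no binary or ordinal form defined

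*Protocol article*

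**What the plan says.** The last analysis paragraph of Data collection and statistics says that "a multiple logistic regression analysis (manual stepwise method) will be performed in order to obtain an associative model". The outcomes it names are pain, tolerance and satisfaction with the intervention. The explanatory side is left open: "the rest of the covariates potentially considered as such". It gives no event, cut-point or ordinal form, and no rule for entering or removing variables.

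Table 2 (Other variables) and its footnotes give the scales. Pain is a "VAS for pain, where 0 indicates no pain, 1–3 mild pain, 4–6 moderate pain, 7–8 severe pain, and 9–10 excruciating pain". Tolerance and satisfaction with the intervention use a "VAS, where 1 represents the minimum value and 10 the maximum value", with no bands.

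The third secondary objective (Objectives and study design) lists the explanatory variables. After demographics and personal history it names "assigned arm, type of IR procedure, anxiety related to the IR procedure, knowledge and understanding of the IR procedure, type of anesthesia". Sedation is on the list too. Per Table 2, anxiety and knowledge are measured at screening, after the radiologist consultation (experimental arm only) and on the procedure day before the procedure. Anesthesia type and sedation level are recorded after the procedure. The article does not say which anxiety or knowledge measurement enters the model.

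The second secondary objective separately compares the same three outcomes. The statistics section assigns t-tests, or nonparametric tests if the data are not normal, to quantitative variables.

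**The concern.** Three features of the stated method work against the third secondary objective.

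- **Outcome form.** Binary logistic regression needs a yes/no outcome, and these are graded scores. Someone must choose a cut-point, and the article fixes none. Any cut discards information, and the results depend on where it falls. The five pain bands do not define one split, and tolerance and satisfaction have no bands at all.
- **Selection.** Manual stepwise selection from an open-ended list yields p-values and intervals that take no account of the selection. Variables with no real association can then be reported as predictors of pain, tolerance or satisfaction.
- **Covariate timing.** Assigned arm is a candidate beside variables that arise after randomization (anesthesia, sedation) or may do so (anxiety, knowledge, if the procedure-day values are used). Knowledge and anxiety are also among the trial's main outcomes. With such variables in the model, the arm coefficient is no longer the total effect of assignment.

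**Working it through.** **1. The plan's own figure.** The only stated calculation is the sample size for the knowledge score: difference 1, SD 3.5, two-sided alpha 0.05, power 80%, 10% loss.

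- n per arm = 2 × (1.960 + 0.842)² × 3.5² / 1² = 192.3, that is 193 evaluable.
- 192.3 / 0.9 = 213.7, that is 214, as stated.

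The figure reproduces, and the present point does not touch it. Evaluable total: 428 × 0.9 = 385.

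**2. Information lost by dichotomizing.** For a normal score split at its median, relative efficiency is 2/π = 0.637, so 385 patients carry the information of about 385 × 0.637 = 245. This is an illustration. The article states neither normality nor a median cut.

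The same loss in terms of power, for a comparison of two equal groups of 193, borrows the planning effect d = 1/3.5 = 0.2857, because no SD is given for these VAS outcomes. If a share p₀ of one group exceeds the cut, the share in the other is p₁ = 1 − Φ(z₁₋ₚ₀ − 0.2857).

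| Analysis | p₀ | p₁ | Power, 193 per group | Evaluable per group for 80% |
|---|---|---|---|---|
| Full score | – | – | 80.1% | 193 |
| Dichotomized | 0.50 | 0.612 | 60.5% | 306 |
| Dichotomized | 0.30 | 0.406 | 58.5% | 320 |
| Dichotomized | 0.20 | 0.289 | 53.1% | 364 |
| Dichotomized | 0.10 | 0.160 | 41.4% | 498 |

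The median row agrees with the efficiency figure: 193/306 = 0.63. Less central cuts lose more.

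**3. Stepwise selection.** Candidates, from the third secondary objective with the detail in Table 2: four demographic (sex, age, marital status, education), four history items, arm, procedure type, anxiety, knowledge, anesthesia and sedation. Total 4 + 4 + 6 = 14. Counting only the headings in the objective gives 8.

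If no candidate is related to the outcome, candidates are independent and the threshold is 0.05:

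- 8 candidates: 1 − 0.95⁸ = 0.34
- 14 candidates: 1 − 0.95¹⁴ = 0.51

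A simulation of backward selection in logistic regression (386 patients, no true associations, 400 runs for each count) kept at least one variable in 34% of runs with 8 candidates and 53% with 14. With 14, it kept 0.74 null variables on average. These rates are per outcome, and there are three outcomes.

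**4. Arm coefficient beside later variables.** This is an illustration with assumed paths, in roughly SD units: arm raises knowledge by 0.2857 and lowers anxiety by 0.2857 directly; knowledge lowers anxiety by 0.3 per unit; anxiety raises pain by 0.4 per unit; arm lowers pain by a further 0.1 directly.

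- Total arm effect = 0.4 × (−0.2857 − 0.3 × 0.2857) − 0.1 = −0.25.
- With knowledge and anxiety in the model, only the direct part remains: −0.10.

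Simulation gave the same two values. The size depends wholly on the assumed paths. What carries over is that the two coefficients answer different questions.

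**The case against.** The strongest reply has four parts.

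- **Logistic regression can be made to work.** An ordinal logistic model takes a 10-point score directly, and a binary one is usable with a justified cut-point. This stands: a reader might infer that logistic regression cannot fit these outcomes, and the article does not support that. The defect is that no form is defined.
- **An article may leave cut-points to the full protocol or analysis plan, which are not shown.** This stands for the cut-point itself, so it cannot be concluded that one will be chosen after seeing the data. It does not cover the model class and the stepwise method, which the article states and which are poorly suited to these scores.
- **The model is called associative, and the second secondary objective already compares these outcomes with tests for quantitative data.** This stands and matters. A reader might infer that the trial's estimate of the arm effect on pain, tolerance or satisfaction will be wrong. The article does not offer this model's arm coefficient as that estimate.
- **The covariates are not shown to be mediators.** This stands in part. Screening values of anxiety and knowledge would be baseline covariates. Anesthesia and sedation are recorded after randomization, but nothing in the article says the intervention is meant to change them.

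An objection to stepwise selection might also be called preference in an exploratory model. But with significance set at 0.05 and no allowance for selection, the printed p-values would not mean what they appear to mean.

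**Conclusion.** The point holds as a weakness of the stated method for one secondary objective. The article commits to manual stepwise logistic regression for three graded scores without defining a binary or ordinal outcome.

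If run as binary, the best-case loss is about 36% of the information (normal score, median split), and more with a less central cut. Selection from about 14 candidates gives roughly a 51% chance per outcome of at least one false entry, and 34% if only 8 are counted. Both figures assume independent candidates and a 0.05 entry threshold; the article gives no entry rule for the manual procedure. The power and attenuation figures are illustrations, not estimates for this trial.

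The point goes no further. The primary outcomes, the sample size and the separate between-arm comparison of the same scores are unaffected. Whether the arm coefficient is over-adjusted depends on which covariates, measured when, are in the model, and the article leaves this open for anxiety and knowledge.

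**What to change.** 1. Replace the stepwise logistic model with multiple linear regression (robust standard errors) or proportional-odds regression on the full VAS score, for each of the three outcomes.
2. Name one covariate set in advance and enter it together, with no stepwise selection.
3. State which measurement of anxiety and knowledge is used.
4. If procedure-day anxiety or knowledge, anesthesia or sedation are in the model, say that its arm coefficient is not the intervention effect. Take that effect from the second-objective comparison, or from a model with only arm, procedure type and pre-randomization variables.

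This changes wording only and needs no new data, patients or visits. The downside is a less compact final model.
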